## 5.8 Baseline Angiography

Following intracoronary injection of nitroglycerin or isosorbide dinitrate, a baseline angiography of the target vessel must be performed in at least 2 orthogonal views, presenting the target lesion free of foreshortening or vessel overlap. In addition to the clinical routine, OCT and IVUS including IVUS VH documentation should also be done pre-procedure. Please see the Core lab angiographic OCT, and IVUS acquisition guidelines for more details.

## 5.9 Index Procedure

All study investigators and site personnel involved in the clinical trial have to sign the Site Signature and Responsibility log and provide signed and dated curriculum vitae (CV).

Implanting physicians and study investigators will be thoroughly trained by the study sponsor on the study protocol, the device and procedures prior to clinical investigation procedure.

The number of implanting physicians will be limited to investigators who are trained on the CIB, the consensus paper (75), the "4 P" program of BIOTRONIK AG and the instructions for use.

Subject preparation and percutaneous access should be performed according to the standard hospital practice.

The procedure begins once percutaneous access has been made.

### 5.9.1. Lesion Access and Pre-dilatation

Lesion access is up to the discretion of the investigator.

Pre-dilatation of the target lesion is mandatory. A 6F guiding catheter or larger should be used. The use of drug coated balloons or rotational atherectomy device is NOT allowed.

The scaffold system is compatible with most guidewires. The target lesion should be crossed with a 0.014" guide wire.

- Pre-dilatation with a non-compliant balloon with a 1:1 balloon-to-artery ratio is mandatory.
- The balloon should expand fully.
- The residual stenosis before DREAMS 3G implantation is required to be  $\leq 20\%$ , confirmed by any method.

### 5.9.2. Scaffold Implantation

The scaffold implantation and sizing should be performed in accordance with the IFU. The scaffold length should cover the target lesion from normal reference vessel diameter (RVD) proximal to normal RVD distal to assure full coverage of the lesion.

#### Device Diameter:

2.5 mm: RVD 2.5 - 2.7mm

3.0 mm: RVD 2.7 - 3.2mm

3.5 mm: RVD 3.2 - 3.7mm

4.0 mm: RVD 3.7 - 4.2mm

**Device Length:**

13 mm: Lesion Length  $\leq$ 11mm

22 mm: Lesion Length  $\leq$ 20mm

30 mm: Lesion Length  $\leq$ 28mm

Only one clinical investigation scaffold should be used per lesion.

After scaffold implantation an angiography must be performed. Following intracoronary injection of nitroglycerine or isosorbide dinitrate, angiograms should be made in the exact same 2 orthogonal views as pre-scaffolding using the same catheter type and size.

**5.9.3. Post-dilatation**

Post-dilatation with a non-compliant balloon of up to 0.5 mm bigger than the nominal scaffold size and at high pressure (>16 atm) is mandatory.

- DREAMS 3G expansion limit is 0.6 mm beyond nominal scaffold size.
- The use of cutting/scoring or drug coated balloons is NOT allowed.

After post-dilatation, all subjects will undergo the routine angiography as well as additional IVUS (including IVUS VH documentation) and OCT assessment. The angiographic, IVUS and OCT acquisition post-procedure is described in the corelab guidelines.

**5.10 Treatment Failure and Bailout Situation**

For dissections occurring during, or immediately after implantation of DREAMS 3G, a second DREAMS 3G may be used, not overlapping with initial one but implanted end-to-end.

If another stent needs to be implanted in the immediate vicinity of an already implanted DREAMS 3G , e.g., clinically significant residual stenosis or restenosis, up to 120 days post procedure, only a DREAMS 3G coronary scaffold system should be used.

Contact of the DREAMS 3G with an uncoated or polymer coated stent up to 120 days may result in accelerated resorption of the DREAMS 3G and undesired local and downstream effects. After 120 days any other stent type may be used.

The treatment with an additional stent or scaffold must be documented angiographically, and by IVUS and OCT images in following the same process described in the previous treatment section.

When a second device needs to be implanted, the “4Ps” need to be observed.

### 5.11 Post Procedure until Discharge

Between end of procedure and hospital discharge, following examinations have to be performed:

- A 12-lead ECG within 6-24 hours post-procedure or at discharge, whichever comes first.
- Cardiac biomarkers CK, CK-MB and Troponin between 6-24 hours post-procedure or at discharge, whichever comes first (assessment of CK-MB is mandatory)

**If CK, CKMB and/or Troponin elevation is noted post-procedure, CK, CK-MB and Troponin measurements should be performed every 8 hours and documented in the CRF until values have returned to normal or until discharge, starting from when the first elevation is noted.**

*Note:* Every effort must be made to obtain cardiac biomarkers values within the specified time ranges. Results of all cardiac biomarkers measurements, even measurements performed outside the time range must be documented on the CRFs.

Adverse events and device effects, concomitant medications, and any interventional treatment that occurred since the procedure must be recorded before discharge.

A patient implantation card must be given to the patient prior to discharge. The card documents that the patient has received a DREAMS 3G device with the corresponding

device information. The patient must be instructed to carry the patient implantation card at all times with him.

## 5.12 Follow-Up Visits

All enrolled subjects will be followed through hospital discharge and will undergo follow-up evaluations at following time points:

| Follow-up visit | Visit window            |
|-----------------|-------------------------|
| 1 month         | 30 days $\pm$ 7 days    |
| 6 months        | 180 days $\pm$ 30 days  |
| 12 months       | 365 days $\pm$ 30 days  |
| 24 months       | 730 days $\pm$ 30 days  |
| 36 months       | 1095 days $\pm$ 30 days |

### 5.12.1 One Month Clinical Follow-Up

All subjects will be contacted for a clinical evaluation at 30 days post-procedure ( $\pm$  7 days), including:

- Assessment of the ischemic/angina status (CCS, Braunwald or silent ischemia),
- Any adverse- or serious adverse events or device deficiencies
- Anti-platelet/anti-coagulant medical therapy

The visit can be performed by phone or as in hospital visit.

### 5.12.2 6 Months Clinical Follow-Up and Imaging follow-up

All subjects will be contacted for clinical and imaging evaluation at 180 days post-procedure ( $\pm$  30 days), including:

- Assessment of the ischemic/angina status (CCS, Braunwald or silent ischemia),
- Any adverse- or serious adverse events or device deficiencies
- Anti-platelet/anti-coagulant medical therapy
- Angiography, IVUS (including IVUS-VH documentation) and OCT.  
These assessments will be done in addition to the clinical routine.
- ECG (according to hospital's standard of care)

For women of child-bearing potential < 55 years, a pregnancy test must be performed before the 6-month angiographic examination.

### 5.12.3 12 Months Clinical Follow-Up and Imaging follow-up

All subjects will be contacted for clinical and imaging evaluation at 365 days post-procedure ( $\pm$  30 days), including:

- Assessment of the ischemic/angina status (CCS, Braunwald or silent ischemia),
- Any adverse- or serious adverse events or device deficiencies
- Anti-platelet/anti-coagulant medical therapy
- Angiography, IVUS (including IVUS-VH documentation) and OCT.  
These assessments will be done in addition to the clinical routine.
- Vasomotion will be assessed angiographically with Acetylcholine followed by Nitroglycerine, if subject consents. This is in addition to the clinical routine.
- ECG (according to hospital's standard of care)

For women of child-bearing potential < 55 years, a pregnancy test must be performed before the 12-month angiographic examination.

### 5.12.4 24 and 36 Months Clinical Follow-Up

All subjects will be contacted yearly for clinical evaluation at:

730 days post-procedure ( $\pm$  30 days) and  
1095 days post-procedure ( $\pm$  30 days)

The following assessment will be performed:

- Ischemic/angina status (CCS, Braunwald or silent ischemia),

- Any adverse- or serious adverse events or device deficiencies
- Anti-platelet/anti-coagulant medical therapy

The visits can be performed by phone or as in hospital visit.

#### 5.12.5 Vasomotion

If subject consents, a vasomotion test will be performed at 12 months follow up in order to obtain additional information on vasoreactivity of the vessel as well as vessel movement throughout absorption of the DREAMS 3G.

All anti-anginal agents that influence vasomotor tone, including long-acting nitrate, calcium-channel blockers, and beta-blockers, should be withheld for at least 48 h before coronary angiography, except for sublingual nitroglycerin as needed.

A coronary angiography will be taken prior to injection of acetylcholine (ACH) in the same two orthogonal views used during baseline procedure.

Diagnostic left / right heart catheterization and coronary angiography will be performed by a standard percutaneous approach. A 6-F diagnostic catheter will be introduced into the left main or right coronary artery, depending on the vessel studied. To ensure that the segments were fully bathed by the infusion of acetylcholine (ACH), the tip of the infusion catheter will be placed 8 -12 mm proximal to the proximal border of the scaffolded segment. To avoid wire induced coronary spasm, the wire will be removed.

Vasomotor reactivity will be estimated by infusing incremental doses of ACH into the coronary artery using an infusion catheter (i.e. Finecross MG; Terumo).

ACH should be admitted in different concentration.

- ACH1 (low dose): 0.36 µg/mL
- ACH2 (middle dose): 3.6 µg/mL
- ACH3 (high dose): 18 µg/mL

Speed of infusion should be 2 mL/min. Duration of infusion should be around 3 minutes. Contrast injection should be filmed after 3 minutes of i.c. infusion of ACH.

When the maximum dose is reached, an intracoronary bolus injection of nitroglycerin (200 µg) will be administered followed immediately by angiography in the same two orthogonal views used during baseline procedure.

Throughout each infusion, the heart rate, systemic arterial pressure, and ECG will be monitored continuously

End-diastolic images for each segment will be chosen and analyzed with the automated edge detection program by QCA. The scaffolded segment and the 5-mm proximal and distal to the site of scaffolding will be studied. Changes in coronary diameter in response to ACH and nitrate coronary infusion will be expressed as percent changes versus baseline angiograms. The mean lumen diameters will be measured by QCA

#### 5.12.6 Angiographic, IVUS and OCT Follow Up

Several studies have confirmed the bias of increased TLR events introduced by protocol catheterization (120,121). With this comes the dilemma of whether subjects would have remained stable for a long time without further revascularization or would soon have become symptomatic if revascularization had not been performed. Although attempts have been made to stratify TLR driven by protocol catheterization, even independent adjudication is very complex in this setting (122).

Thus, the Academic Research Consortium (ARC) consensus for DES evaluation is to primarily assess clinically driven TLR within a time interval that precedes any protocol-mandated repeat catheterization and include subsequent TLR in secondary analyses, with best adjudication as to clinical need (123). Thus every effort should be made, to conduct the clinical evaluation prior to the angiographic evaluation.

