| Secondary Endpoints       | 
Clinical
 

Target Lesion Failure (TLF*) at 1, 6, 12 months and annually thereafter until 36 months post procedure

Cardiac death at 1, 6, 12 months and annually thereafter until 36 months post procedure (according to ARC-1 definition)

Target vessel MI at 1, 6, 12 months and annually thereafter until 36 months post procedure**

Clinically driven target lesion revascularization at 1, 6, 12 months and annually thereafter until 36 months post procedure

Clinically driven target vessel revascularization at 1, 6, 12 months and annually thereafter until 36 months post procedure

Definite and probable scaffold thrombosis rate at 1, 6, 12 months and annually thereafter until 36 months post procedure (according to ARC-2 definition)

 |    |    |    |    |                           |     |   |   |   |   |   |     |   |   |   |   |   |

|                  |                                                                                                                                                                                                                                                                                                                                                                                                                                                                                                                                                                                                                                                                                                                                                                                                                                                                                                                                                                                                                                                                                                                                                                                                                                                                                                                                                                                                      |

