#### 4.8 Secondary Endpoints

##### Clinical

- Target Lesion Failure (TLF\*) at 1, 6, 12, and annually up to 36 months follow up

- Cardiac death at 1, 6, 12, and annually up to 36 months follow up (according to ARC-1 definition)
- Target vessel MI at 1, 6, 12, and annually up to 36 months follow up\*\*
- Clinically driven target lesion revascularization at 1, 6, 12, and annually up to 36 months follow up
- Clinically driven target vessel revascularization at 1, 6, 12, and annually up to 36 months follow up
- Definite and probable scaffold thrombosis rate at at 1, 6, 12, and annually up to 36 months follow up (according to ARC-2 definition)
- Procedure success: achievement of a final diameter stenosis of <30% by QCA, using any percutaneous method, without the occurrence of death, Q-wave or non-Q-wave MI, or repeat revascularization of the target lesion during the hospital stay.
- Device Success: final residual diameter stenosis of <30% by QCA, or visual assessment using the assigned device only with:
  - Successful delivery of the scaffold to the target lesion
  - Appropriate scaffold deployment
  - Successful removal of the delivery system

\*defined according to ARC-2 and ARC-1 definition.

\*\* periprocedural MIs will be adjudicated according to SCAI-definitions and ARC-2 definitions

Secondary clinical endpoints were selected as per recommendations of the American College of Cardiology (ACC) and the American Heart Association (AHA) (Ref. ACC/AHA CLINICAL DATA STANDARDS: "", JACC VOL2014 ACC/AHA Key Data Elements and Definitions for Cardiovascular Endpoint Events in Clinical Trials. 66, NO. 4, 2015) (119).

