**CLINICALLY DRIVEN TARGET LESION REVASCULARIZATION (TLR) (123)**

Any clinically-driven repeat percutaneous intervention of the target lesion including 5mm proximal and 5mm distal from the edge of the scaffold, or bypass surgery of the target vessel that was performed for a clinical indication and was due to restenosis or closure of the target lesion.

Clinically-driven revascularizations are those in which the subjects has a positive functional clinical investigation, ischemic ECG changes at rest in a distribution consistent with the target vessel, or ischemic symptoms and an in-lesion diameter stenosis  $\geq 50\%$  by QCA. Revascularization of a target lesion with an in-lesion diameter stenosis  $\geq 70\%$  (by QCA) in the absence of the above-mentioned ischemic signs or symptoms is also considered clinically-driven. In the absence of QCA data for relevant follow-up angiograms, the clinical need for revascularization is adjudicated using the presence or absence of ischemic signs and symptoms.

Non-clinically driven repeat target lesion revascularizations are those in which the subjects undergoes a non-emergent revascularization for a diameter stenosis  $< 50\%$  (by QCA). Non-emergent repeat target lesion revascularization for a diameter stenosis  $< 70\%$  (by QCA) in subjects without either a positive functional clinical investigation or angina are also considered non-clinically driven.

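### Section 5.12.6 cites assessing clinically driven TLR before scheduled angiography, but no TLR or TLF reading from 6 months on has a pre-angiogram cut-off, so these rates can include protocol-prompted events

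*Protocol*

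**What the plan says.** Protocol section 5.12.6 names the problem directly: "Several studies have confirmed the bias of increased TLR events introduced by protocol catheterization". It adds that "even independent adjudication is very complex in this setting". It then reports the ARC consensus in these terms: "primarily assess clinically driven TLR within a time interval that precedes any protocol-mandated repeat catheterization and include subsequent TLR in secondary analyses". That consensus also asks for careful judgement of whether the later procedures were clinically needed. The instruction that follows concerns visit order only: "Thus every effort should be made, to conduct the clinical evaluation prior to the angiographic evaluation".

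The endpoints are set elsewhere. Section 4.8 lists "Clinically driven target lesion revascularization at 1, 6, 12, and annually up to 36 months follow up", with the same reading times for clinically driven TVR. The Synopsis has "Target Lesion Failure (TLF*) at 1, 6, 12 months and annually thereafter until 36 months post procedure". Section 7.3 analyses these endpoints by Kaplan-Meier and ties event rates to the visit window, with 365 ± 30 days as its example.

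The scheduled imaging is in sections 4.4, 5.12.2 and 5.12.3. At 6 and at 12 months all subjects are to have "Angiography, IVUS (including IVUS-VH documentation) and OCT". The visit windows in section 5.12 are 180 ± 30 and 365 ± 30 days.

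Appendix 2 defines clinically driven TLR. Revascularization of a target lesion with at least 70% stenosis by QCA "in the absence of the above-mentioned ischemic signs or symptoms is also considered clinically-driven". Non-emergent revascularization below 50% stenosis, or below 70% without a positive functional test or angina, is classed as not clinically driven. Both TLF definitions (ARC-1 and ARC-2) include clinically driven TLR.

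**The concern.** The protocol recognises a bias and cites a consensus that deals with it by timing. It then fixes its clinical endpoints without that timing. A subject with no symptoms who has a tight stenosis on the scheduled 6-month film, and is treated for it, enters the data as a clinically driven TLR and as a TLF. Without the scheduled film that event might not have occurred, or might have occurred later.

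TLF and TLR are the main clinical results beside late lumen loss in a study meant to support CE approval. With at most 115 subjects and low event rates, a few such events would change the reported figure visibly. The documents contain a related example. In BIOSOLVE-I (section 1.1.2), treating a stenosis during the 12-month follow-up angiography caused one peri-procedural target vessel MI, and TLF rose from 4% at 6 months to 7% at 1 year. That event was an MI, and it was not related to the original target lesion, so it is not an instance of the TLR problem. It does show that an intervention at a follow-up film can shift TLF in a small trial.

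**Working it through.** The protocol states no expected TLR or TLF rate for this trial, so there is no figure to reproduce. The check compares dates, then definitions, then the weight of one event.

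**Step 1: reading times against scheduled films** (windows from section 5.12)

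- First scheduled angiogram: 180 − 30 = day 150 to 180 + 30 = day 210.
- Second scheduled angiogram: 365 − 30 = day 335 to 365 + 30 = day 395.

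| Reading | Window (days) | Scheduled films that can fall before or within it |
|---|---|---|
| 1 month | 23–37 | none |
| 6 months | 150–210 | first |
| 12 months | 335–395 | first (already done) and second |
| 24 months | 700–760 | both |
| 36 months | 1065–1125 | both |

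A reading precedes every in-window scheduled film only if it ends before day 150. Of the five readings, only the 1-month one does (latest day 37).

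**Step 2: what the visit-order rule can and cannot remove** (definition from Appendix 2)

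- Stenosis below 50%, non-emergent: not clinically driven. The definition screens it out.
- Stenosis from 50% to below 70%: clinically driven only with ischemic symptoms, ECG changes or a positive functional test. Recording clinical status before the film protects this classification.
- Stenosis of 70% or more: clinically driven even when silent. A clean clinical evaluation beforehand does not alter the count.

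The route for a protocol-prompted event is therefore mainly the last band. Visit order at 6 months also does nothing to separate, in the later cumulative rates, events that the 6-month film prompted.

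**Step 3: weight of one event** (enrolment from sections 4.4 and 7.2)

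Crude contribution = 100 × k / N, for k protocol-prompted events:

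- N = 115, k = 1: 100 / 115 = 0.87 points.
- N = 104, k = 1: 100 / 104 = 0.96 points.
- N = 115, k = 3: 300 / 115 = 2.6 points.

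The values of k are assumptions. For scale, section 1.1.3 reports three clinically driven TLRs of any origin at 6 months in BIOSOLVE-II and BIOSOLVE-III pooled (184 enrolled), so k = 3 in 115 subjects would be high at that reading. A Kaplan-Meier estimate with fewer subjects at risk gives slightly more weight per event.

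**Step 4: what is not touched**

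The primary endpoint is a lumen measurement, not a count of revascularizations. The stopping rules in section 9.7 use only the first 30 days of each subject's follow-up, well before day 150.

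**The case against.** The strongest reply is that the protocol breaks no rule of its own. The consensus is cited as rationale; the instruction is clinical evaluation first, and it is carried through. All TLR and TLF endpoints are already secondary and untested, which partly matches the consensus placing later TLR in secondary analyses. The 70% rule cites the same source as that consensus. The Clinical Events Committee adjudicates finally (section 8.1.2), and the definition removes the mildest lesions. Section 7 defers the full analysis description to an SAP that is not at hand and may contain a pre-angiogram analysis.

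Much of this stands, and it limits the point. What remains is that section 5.12.6 itself calls adjudication very complex here, that its one rule does not reach the silent lesion of 70% or more, and that sections 4.8 and 7.3 give no reading between 1 month and the first scheduled film.

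A reader might infer four stronger things, none of which the documents support:

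- **That the rates will be inflated by some number of points over the pooled BIOSOLVE-II/III rate of 3.3%.** BIOSOLVE-II, 123 of the 184 pooled subjects, already had angiography at 6 months, performed in 113 implanted subjects. Adding a further percentage to that rate would count the effect twice. BIOSOLVE-III had scheduled angiography at 12 months, and section 1.1.3 reports no added TLF between 6 and 12 months.
- **That protocol-prompted events cannot be separated.** Events are dated, scheduled imaging is a distinct visit item, and section 5.12.7 handles clinically driven films separately. The protocol plans no separation, but the data would allow a cut-off by date.
- **That the booking date decides which side of day 180 an event falls on.** Section 7.3 points to the visit window, not to a day-180 cut-off.
- **That visit order has no effect.** It helps in the 50% to below 70% band.

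**Conclusion.** The point holds as an inconsistency within the protocol. Section 5.12.6 identifies the bias and cites a timing remedy, while the endpoints in sections 4.8 and 7.3, read with Appendix 2, do not use it. The TLF, clinically driven TLR and clinically driven TVR rates at 6, 12, 24 and 36 months can include revascularizations first prompted by the scheduled film. Whether they will, and how often, cannot be told from the documents. Each such event is worth about 0.87 percentage points at full enrolment, assuming no censoring.

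The consequence is limited to the interpretation of secondary, descriptive results. This is an inexpensive improvement and not a defect in the primary analysis. The conclusion assumes that the unseen SAP does not already name a pre-angiogram analysis. If it does, what remains is to align the protocol text and to record what prompted each revascularization.

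**What to change.** Reconcile section 5.12.6 with sections 4.8 and 7.3 and Appendix 2:

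1. Keep the all-events rates at all five reading times.
2. Add a named analysis of TLF, clinically driven TLR and clinically driven TVR, censored at each subject's first scheduled angiogram. State that a revascularization done at that session falls after the cut-off. A clinically driven film at 3 to 6 months that stands in for the 6-month angiogram under section 5.12.7 must not trigger the cut-off, since the event behind it is one the analysis should keep.
3. Add one field to the eCRF and the Clinical Events Committee form: was the revascularization first prompted by scheduled imaging, yes or no. Report the 12-, 24- and 36-month rates with and without those events. State how an MI complicating such a revascularization is counted in TLF.

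The cost is one field and extra tables, with no added visits or procedures. The censored analysis has slightly shorter follow-up, most of all in subjects imaged early in the window. It should not replace the all-events rate, which remains the one comparable with BIOSOLVE-II and BIOSOLVE-III, because those studies also had scheduled angiography.
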